#### Outcome measures

Because we are testing an implementation intervention and our ASD EBI have been shown to be effective in our large-scale effectiveness trials, our primary measures are related to provider implementation (training completion/fidelity). However, consistent with Hybrid, type 3 designs, we will collect child outcome data as secondary outcome measures (within session behavior; standardized measures). Outcomes will be collected for leaders and providers using the following timeframes: Baseline (BL—initial program/district enrollment), Pre (PRE—prior to EBI Training), Post training (POST—6 months after initiation EBI training), and Follow-Up (12 months post PRE). Parents will complete child measures at PRE and POST as children may not remain with the same provider or be receiving services at follow-up. Data will be collected by administering a brief battery of measures (including demographic measures for all participants) via on-line survey or phone interview. The outcome constructs include implementation outcomes (provider and child) as well as measurement of the specific mechanisms of change expected from the implementation intervention. Refer to Table 3 for specific outcome measures and timing.

**Table 3 Tab3:** Study measures

Purpose (aim)	Construct	Measure/indicators	Timeframe			
			BL	Pre	Post	FU
Outcomes (aim 1)	Training completion	Provider training/consultation completion (based on trainer-rated attendance tracking)			X	
	Provider fidelity	Fidelity of ASD EBI (*also collected mid-training for total of 3 obs.*)		X	X	.
	Child improvements	Child session behaviors (disruptive, engagement)		X	X	
		Child symptom improvement (ECBI [AIM HI]/PDDBI [CPRT])		X	X	
Mechanisms of change (aims 2, 3)	Provider engagement	Training/consultation attendance (trainer rated)			X	
		Adherence to training requirements (video submissions, forms)			X	
	Provider attitudes	Evidence-Based Practice Attitudes Scale (EBPAS)		X	X	X
		Adapted motivation inventory [116]		X	X	X
	Impl. Leadership & Climate	Implementation Leadership Scale (leaders and providers) [98]	X	X	X	X
		Implementation Climate Scale [117] (leaders and providers)	X	X	X	X
	Implementation support use	Assessment of implementation supports strategies	X	X	X	X
Moderators (aim 3)	Background/experience	AIM HI & CPRT Background Questionnaire (leaders & providers)	X (L)	X (P)		
	Org. structure	Program/District Structure Questionnaire	X			

#### Provider fidelity measures

Provider ASD EBI (AIM HI/CPRT) fidelity is the primary study outcome. Provider fidelity will be based on ratings by trained observers blind to study condition and time frame. Fidelity ratings are designed to capture provider use of the core EBI strategies included in the AIM HI and CPRT protocols. Fidelity will be rated with the target child at PRE, mid training, and POST. Fidelity will be coded based on video recordings of sessions/activities using our established procedures for video data collection. AIM HI Fidelity includes 16 Adherence items reflecting expected within-session therapist behaviors in three categories (Structuring Sessions for Skill-Building, Motivating Children, Active Teaching). These are rated separately for parents and children. There are also 4 Effectiveness Items (e.g., session is organized and structured). The inter-rater reliability of these items are high (*M* = .77, range = 0.65 to 0.90 based on 299 double-coded sessions). Furthermore, all individual and composite scores for therapists trained in AIM HI are significantly higher than therapists delivering usual care (based on over 600 coded sessions), providing support for the discriminant validity of the measure. Sessions recordings will be submitted online prior to training and monthly during the 6-month training/consultation period*.* CPRT fidelity includes 15 adherence items reflecting expected within-session teacher behaviors in three categories (maximizing student motivation, facilitating student responding, providing appropriate consequences). There are also 4 effectiveness items (e.g., manages distractions in the teaching environment). All items are rated on a 1–5 Likert scale after observing the complete activity with 1 being teacher does not implement or implements correctly less than 30% of the time to 5, teacher implements correctly throughout the session (100%). The inter-rater reliability of these items are high (*M* = .73, range = 0.50–0.90 based on 240+ double-coded sessions).

#### Coder training

Coders will be trained to code fidelity for one of the EBI (AIM HI or CPRT), and child session behavior. All coders will be blind to treatment groups (STAN, TLI; TIPS; TLI + TIPS) and time frame. They will be trained to 80% reliability across 6 videos before coding for the study. If there is less than 80% agreement between the investigator and the coder, additional training will be provided until agreement is achieved. Twenty-five percent of all video samples will be scored by a second person for the purpose of monitoring reliability of coding.

## Data analysis

### General data analytic plan for aims 1–3

All data analytic strategies will follow the recommendations of Brown et al. and the Prevention Science and Methodology Group for randomized field trials [103]. Preliminary data screening and cleaning will require examination of the data distributions for normality and missing data patterns at both the univariate and multivariate level. Preliminary data analysis will also be conducted to determine if there are significant differences between the two studies (CPRT and AIM HI) on target variables. If no significant differences are found, data from the two studies will be integrated to maximize the available data for specific analyses. In the case that outcome variables differ by study, variables representing study will be included as a covariate in all models. Some of the target outcome variables in the two studies were measured using different scales (e.g., AIM HI and CPRT Fidelity). To ensure comparability on these measures, variables will be converted to *z*-scores before statistical comparisons are made. Hierarchical linear modeling (HLM) will be used as the primary, but not only, statistical model due to the nested structure of the data and when the outcome measure is at the provider/outcome level: repeated measures [level-1] nested within providers/children [level-2] nested within program/district [level-3]). Possible clustering effects will initially be estimated by examining intraclass correlation coefficients to determine if accounting for clustering is necessary. All analyses will use an intent-to-treat approach for the TEAMS groups. Because the TEAMS condition variable will contain four groups, three dummy-coded variables will be created and used as predictor variables in target statistical models. To account for the different type of leader at the program/district level, a level-3 binary variable representing whether or not the agency/district leader is a director or a first-level leader will be used in all analyses. Covariates (e.g., baseline scores) may be included in the models to adjust for nonequivalence at baseline and to minimize bias. All analyses will use AR(1) to model a first-order autoregressive correlation structure for the repeated-measures data. Missing data common to longitudinal designs is readily incorporated in HLM if the data can be assumed to be missing at random. However, because there is no statistical test of data that is missing at random [104], all data analysis will also employ selection models [105] to model relationships of interest for the data missing not at random mechanism, as recommended by Little and Rubin [106]. Of interest in some of proffered hypotheses are the differences in target outcomes between the TEAMS groups over time. The TEAMS groups will be statistically compared when a significant cross-level (Time X TEAMS Group) interaction is evident using the statistical methods of Preacher, Curran, and Bauer [107].

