## Method

This Hybrid, type 3 implementation/effectiveness trial will use a cluster randomized factorial dismantling design to examine the independent and combined effectiveness of TLI and TIPS. MH programs (AIM HI study) and School districts (CPRT study) from San Diego, Sacramento, and LA Counties will be randomized to one of four conditions (STANDARD EBI-specific training only (control condition); TIPS (Motivational Module); TLI (LOCI Implementation Leadership Module) or TIPS+TLI (Combined Modules). Data collection will be coordinated between the two studies and pooled for analyses.

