### Procedures for randomization and data collection

#### Randomization

Programs and districts will be randomized by an independent researcher and stratified by county and study via computer-generated randomization to one of four conditions per study following official study enrollment

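### Study, a randomisation stratum, enters the models only after a significant preliminary test that is a poor basis for pooling; county and a TEAMS-by-study comparison are not named

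*Protocol article*

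**What the plan says.** All passages are in the Protocol article.

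- **Randomization:** programs and districts are allocated "stratified by county and study via computer-generated randomization to one of four conditions per study".
- **General data analytic plan for aims 1–3:** "Preliminary data analysis will also be conducted to determine if there are significant differences between the two studies (CPRT and AIM HI) on target variables". Two branches follow. In the first, "If no significant differences are found, data from the two studies will be integrated to maximize the available data for specific analyses". In the second, "In the case that outcome variables differ by study, variables representing study will be included as a covariate in all models". County appears in neither.
- **Same section, on outcomes measured on different scales (AIM HI and CPRT fidelity is the example given):** "To ensure comparability on these measures, variables will be converted to *z*-scores before statistical comparisons are made". The sample that supplies the mean and SD is not stated.
- **Method (opening paragraph):** "Data collection will be coordinated between the two studies and pooled for analyses", with no condition attached.
- **Specific analyses for aim 3:** the moderators are open lists of participant and organisational characteristics. Study or service setting is not among the examples.
- **Current project and Discussion:** the aims cover effectiveness and mechanisms across settings. The Discussion gives wider generality as a reason for using two service systems, and expects to separate shared from setting-specific elements.

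**The concern.** There are three linked problems.

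1. A factor fixed by the randomisation should be in the model whatever the data show. Here study depends on a p-value and county is not named.
2. The preliminary test compares outcome levels. Pooling rests on whether the TEAMS effect is similar in clinics and schools, which is a different quantity. Neither branch contains that comparison: one appears to leave study out, the other adds a main effect only.
3. Fidelity is the primary outcome, and on it the test result depends on how the z-scores are formed, which is left open.

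At stake is mainly interpretation. A TEAMS effect confined to one service system could be averaged into a single pooled figure under a rule that appears to have checked that pooling was safe. The unconditional pooling in Method also needs reconciling with the conditional rule in the analytic plan.

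**Working it through.** **Inputs.** From Power analyses: alpha 0.05 (two-sided assumed, as sidedness is not stated), power 0.80, d = 0.39, attrition 30%, AR(1) correlation 0.60, ICC 0.04, 8 providers per cluster. From Table 1: 37 clusters and 295 providers per study. From aim 1: three fidelity occasions.

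**The plan's own figure.** VIF = 1 + 7 × 0.04 = 1.28, as stated. Per-arm n for one pairwise contrast = 2(1.96 + 0.8416)²/0.39² = 103.2. The mean of three AR(1) measures has variance (3 + 2(0.6 + 0.6 + 0.36))/9 = 0.68, giving 70.2. Dividing by 0.70 gives 100.3, and × 4 × 1.28 gives 513, against 502 stated (about 2% apart). Other readings of the inputs gave from 430 to over 2,000, so this is the closest reading, not a certain one. The stated sample size is not challenged; the same variance is used below.

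**What the pre-test can see on fidelity.** Simulation with 37 clusters of 8 per study, ICC 0.04, AR(1) 0.6, tests on cluster means, true raw study differences of 0.5 or 1.0 SD, and a TEAMS effect of 0.78 SD at POST in the combined arm of one study only:

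| z-score reference | Overall-mean test rejects | POST test rejects |
|---|---|---|
| Within study, all occasions together | 0% | about 0% |
| Within study, each occasion | 0% | 0% |
| Each study's PRE values | about 10% | about 40% |
| Both studies pooled | 100% | 100% |

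The zeros in the overall-mean column are exact: both study means are 0 by construction. Pooled scoring rejects because the raw difference, which includes any instrument difference, is still there. With unequal time slopes (0.2 and 0.8 SD per occasion), within-study scoring over all occasions still gave 100% rejection at POST.

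**Why level is the wrong target.** With four equal arms, an effect in one arm of one study moves that study's mean by a quarter of the effect: 0.78/4 = 0.195, matching the simulated POST gap of about 0.196 under PRE scaling. An effect of 0.39 moves it by 0.39/4 ≈ 0.10, and a study difference of 0.1 SD was detected in only 17% of simulated trials.

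**Cost of leaving study out, outcome not z-scored.** A POST cluster mean has variance 0.04 + 0.96/8 = 0.16. Omitting a study difference δ adds δ²/4, so the SE ratio is √(1 + δ²/0.64).

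| δ (SD) | SE ratio, formula | SE ratio, simulated | Pre-test detects δ |
|---|---|---|---|
| 0.1 | 1.01 | 1.01 | 17% |
| 0.2 | 1.03 | 1.03 | 56% |
| 0.3 | 1.07 | 1.07 | 90% |
| 0.5 | 1.18 | 1.19 | about 100% |

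Type I error without the term was about 2.5–5%, so the loss is conservative.

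**Power for TEAMS by study.** Effective n per arm with 590 providers = (590/4) × 0.70/1.28 = 80.7. The pairwise SE is √(2 × 0.68/80.7) = 0.130 pooled, 0.130 × √2 = 0.184 within one study, and 0.184 × √2 = 0.260 for the between-study difference. At 0.39, power is 85% pooled, 57% within one study, and 32% for a between-study difference of that size. The difference detectable with 80% power is 2.80 × 0.260 = 0.73.

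**The case against.** The best defence is that this is a condensed article. The z-score reference and the covariate list, including county, may be settled in an analysis plan that is not shown, and baseline covariates are allowed in general terms. The trigger is also broad: read literally, a difference on outcome variables brings study into every model, so an outcome that is not z-scored could restore the term for fidelity too. Stratification roughly balances the arms within study, so no material bias follows. These points stand and limit the size of the problem. They do not change the stated rule.

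Some stronger readings are tempting but unsupported:

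- **That the pre-test can never detect anything on fidelity.** This needs z-scores formed within study and a comparison of overall means, or within-study scoring at each occasion. The article states neither, and under other references differences are detectable.
- **That fidelity suffers both harms at once.** If z-scoring within study silences the test, both study means are 0 and omitting the study main effect costs essentially nothing.
- **That z-scoring erases the time trend.** Only per-occasion scoring would do so, and nothing says it is planned. Arm differences at each occasion would remain.
- **That adjustment would cut the 0.04 ICC substantially.** That ICC comes from AIM HI alone, so it contains no between-study variance. The article gives no figure for variance between counties.
- **That the plan rules out testing TEAMS by study.** It is not named, but the moderator list is open.

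Low interaction power is also a fair point: a non-significant interaction would not justify pooling either.

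**Conclusion.** The point holds as a defect in a stated rule. A stratification factor is made conditional on a significance test, county is not named, and the test does not address whether TEAMS effects are alike in the two systems. On fidelity its result depends on an unstated scaling choice: within-study scoring equalises overall means by construction, and pooled scoring leaves the instruments' scales unreconciled. No TEAMS-by-study comparison is named to support the cross-setting claims.

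The statistical cost is modest. On outcomes that are not z-scored, the SE rises about 1–7% for study differences of 0.1–0.3 SD, in the conservative direction. On fidelity z-scored within study there is essentially no cost. The larger consequence is that the pre-test cannot support the pooled interpretation.

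These sizes assume two-sided testing, the Power analyses inputs with the ICC applied to both studies, and equal arms. The SE figures also assume complete clusters of 8; the power figures allow for 30% attrition.

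**What to change.** - Delete the preliminary test, and make Method and the general analytic plan state the same pooling rule.
- Keep study and county as fixed effects in all models, regardless of significance.
- Standardise each study's fidelity by that study's PRE mean and SD, arms combined, and apply those two constants at PRE, mid-training and POST. This keeps change over time and arm differences visible.
- Report TEAMS-by-study and study-specific estimates with confidence intervals beside the pooled estimate. Label them descriptive and do not use them as a gate for pooling, because power is about 32% for a between-study difference of 0.39.

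The cost is wording and a few program-level degrees of freedom. Study takes 1 and the three counties take 2, so 3 of the 74 − 4 = 70 left after fitting four arms (5 if the six study-by-county cells are used). The sample size does not change. The wording should be settled before outcome data are examined, because the scaling choice determines what any between-study comparison can show.

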
#### Specific analyses for aim 1: test the effectiveness of the TEAMS modules individually and in combination on implementation outcomes when paired with two ASD EBI

To determine if there are significant main effects and interactions between the TEAMS groups on observed therapist fidelity (based on video recorded sessions coded at 3 time points over 6 months), statistical analyses will proceed using the 3-level nested data structure outlined in the General Analytic Plan section. To determine if there are significant differences between the TEAMS groups on observed child behaviors during sessions, statistical analyses will proceed using the 3-level nested data structure outlined in the General Analytic Plan section. To determine if there are differences between the TEAMS groups on child symptoms (EBCI or PDDBI) at 6 months, the 3-level nested data structured will be used.

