#### Specific analyses for aim 2: test the impact of TEAMS modules on leader- and provider-level mechanisms of change

Measurement of leader-level outcomes is of primary interest. Implementation Leadership and Climate scores will be aggregated to the leader level. For this reason, HLM models (or single-level regression models if ICC values suggest clustering is negligible) will be used to test for TEAMS group differences on measures of implementation leadership and climate scores at 6 and 12 months. These analyses will control for baseline scores on these measures. To determine if there are significant differences between the TEAMS groups on therapist attitudes (EBPAS), analyses will proceed using the 3-level nested data structure outlined in the General Analytic Plan. These analyses will control for baseline EBPAS scores.

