### Power analyses

To estimate the sample size needed to detect statistically significant differences between TEAMS groups in the context of the 3-level nested data structure (e.g., aim 1, hypothesis 1), the power program RMASS2 [109] was used. The RMASS2 program is specifically designed to calculate the projected sample size needed for longitudinal data with attrition when a comparison is made between groups. To determine the minimum sample size necessary, several assumptions were made: (1) An alpha level of .05 and a power level of 0.80, (2) an effect size of *d* = .39 (based on the CPRT effectiveness trial ES for impact of training on teacher fidelity), (3) 30% overall attrition rate was specified, and (4) a stationary autoregressive structure (lag 1) was specified for the variance-covariance matrix of the repeated measures, using an autocorrelation value of 0.60. In addition, clustering at the programs/districts level was accounted for via the variance inflation factor (VIF = 1.28): 1 + (*c* − 1) × ICC, where *c* is the average number of providers/children per programs/districts (*n* = 8) and the ICC at the programs/districts level (ICC = 0.04, based on AIM HI therapist fidelity outcome). Given these assumptions, 502 providers/children nested within 63 programs/districts are needed to detect statically significant differences between at least two of the TEAMS intervention groups.

Additional power analyses were conducted to determine the sample size needed to detect a hypothesized mediated effect or moderation of the antecedent to mediator relationship (see Aim 3), which is likely to be the most underpowered effect proposed. This set of power analyses was conducted to determine the minimum necessary sample size to find a statically significant mediated effect from variables presenting the TEAMS groups to a target mediator (e.g., provider attitudes) to a target outcome (e.g., provider fidelity outcome). Using the simulation approach for meditational models of Thoemmes, MacKinnon, and Reiser [110], small effects (*R*^2^ values of 2%) were specified for both the mediator and outcome variables. Accounting for the VIF defined above, 591 providers/children nested within 74 programs/districts are needed to detect statistically significant mediated effect.

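### The general analysis plan lets the observed ICC decide whether the randomised level (program/district) stays in the model, and does not exempt the primary fidelity analysis

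*Protocol article*

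**What the plan says.** The Method section describes a trial that "will use a cluster randomized factorial dismantling design to examine the independent and combined effectiveness of TLI and TIPS", and under Randomization: "Programs and districts will be randomized by an independent researcher and stratified by county and study". The program or district is therefore the unit of allocation, with an average of 8 providers each and one child per provider.

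The general data analytic plan names its default: "Hierarchical linear modeling (HLM) will be used as the primary, but not only, statistical model due to the nested structure of the data". It then adds a preliminary step: "Possible clustering effects will initially be estimated by examining intraclass correlation coefficients to determine if accounting for clustering is necessary". It gives no threshold, no test, and no list of the outcomes to which the step applies.

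For aim 1, fidelity and child session behaviours are handled by reference: "statistical analyses will proceed using the 3-level nested data structure outlined in the General Analytic Plan section". Child symptoms are likewise sent to the three-level structure. The Provider fidelity measures section makes fidelity the primary outcome.

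For aim 2, leadership and climate scores are aggregated to the leader, and "HLM models (or single-level regression models if ICC values suggest clustering is negligible) will be used".

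The Power analyses section assumes an ICC of 0.04, taken from a therapist fidelity outcome, and states that "clustering at the programs/districts level was accounted for via the variance inflation factor (VIF = 1.28", with cluster size 8).

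**The concern.** When whole programs and districts are allocated, variation between them is part of the error against which the conditions must be compared. That follows from the design and does not depend on how large the ICC turns out to be in the sample. A preliminary look at the ICC therefore cannot settle whether the cluster level is needed. A low estimate may simply be imprecise, and removing the level then tests TLI and TIPS against provider-level variance alone. If the true ICC is above zero, standard errors for between-group differences are too small and false positives exceed the nominal rate.

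The document also pulls in two directions. It expects clustering on fidelity and enlarges the sample by 28% for it, but its analysis section leaves room to set that clustering aside after the data are seen. With no stated criterion, that choice would be made post hoc on the primary outcome.

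**Working it through.** **Inputs from the protocol article.** Cluster size 8, 74 clusters (Sample); ICC 0.04, alpha 0.05, AR(1) autocorrelation 0.60, VIF 1.28, 502 providers in 63 clusters for aim 1 and 591 in 74 for mediation (Power analyses); fidelity rated at PRE, mid-training and POST (Provider fidelity measures). Two-sided testing is assumed, since sidedness is not stated.

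**Reproducing the plan's figure.** VIF = 1 + (8 − 1) × 0.04 = 1.28, as stated. Also 502/8 = 62.75, i.e. 63 clusters, and 591/8 = 73.9, i.e. 74 clusters. The planned sample already carries the inflation for clustering.

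**Upper bound: clustering always ignored.** For a between-group comparison of one value per provider:
- Standard error relative to its correct value: 1/√1.28 = 0.88.
- Type I error: 2 × [1 − Φ(1.96/√1.28)] = 2 × [1 − Φ(1.732)] = 8.3%.

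**The screen itself.** This was simulated under the null: 10,000 trials, 74 clusters of 8, four arms, true ICC 0.04, one value per provider, two arms compared. The individual-level test was used when the screen dropped clustering and a cluster-level error term otherwise. The cut-offs are assumptions, because the plan states none.

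| Rule for dropping clustering | Trials in which it is dropped | Type I error |
|---|---|---|
| Estimated ICC < 0.02 | 25% | 5.2% |
| F test of ICC, p > 0.05 | 50% | 6.0% |
| Estimated ICC < 0.05 | 66% | 6.5% |
| Estimated ICC < 0.10 | 98% | 8.0% |
| Never dropped | 0% | 5.0% |

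Monte Carlo error is about 0.2 to 0.3 percentage points. At the ICC the plan expects, a 5% test of clustering misses it in half of all trials.

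**Time-by-group contrast.** Take POST minus PRE change, total variance 1 per occasion, cluster variance 0.04, and within-cluster AR(1) 0.60. PRE and POST are two steps apart, so their within-cluster correlation is 0.60² = 0.36.
- Cluster effect constant over time: it cancels in the change score, the design effect is 1, and ignoring the level leaves about 5% (simulated 4.7%).
- Cluster effect independent at each occasion: cluster variance of change = 2 × 0.04 = 0.08; within-cluster variance = 2 × 0.96 × (1 − 0.36) = 1.2288; ICC of change = 0.08/1.3088 = 0.061; design effect = 1 + 7 × 0.061 = 1.43; type I error = 2 × [1 − Φ(1.96/√1.43)] = 10.1% (simulated 10.1%).

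The document does not say which situation holds, so 8.3% cannot be carried over to this contrast.

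**The case against.** The strongest defence is that the surrounding text favours a three-level analysis. Hierarchical modelling is named as primary because the data are nested. A level-3 indicator of leader type is to enter all analyses, which presupposes a third level. Aim 1 specifies the three-level structure and writes no fallback, and the only explicit single-level fallback is for leadership and climate scores. The authors also evidently do not regard an ICC of 0.04 as trivial, since they paid for it in sample size. All of this stands, and it rules out reading the plan as one that discards clustering. It does not remove the defect: the screening sentence sits in the section that governs aims 1–3, hierarchical modelling is called primary but not the only model, and aim 1 points back to that section without an exemption.

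Three stronger readings are tempting and not supported.
- A reader might take 8.3% as the plan's type I error. It describes always ignoring clustering; the plan describes a screen.
- A reader might quote a larger ICC: at 0.10, always ignoring clustering gives 13.3%. That ICC is not in the document, and at that value an F-test screen drops clustering in only about 3% of simulated trials, giving 5.2%. A lax cut-off of ICC < 0.10 would still give 8.8%.
- A reader might cite the aim 2 fallback as an instance of the error. Those scores are aggregated to the leader, with one leader per program or district, so at a given time point each row is already a cluster and a single-level model is valid.

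**Conclusion.** The point holds as a correctable fault in what the plan permits. The screen should not govern any provider- or child-level comparison of conditions, and as written it is not excluded from the primary one. The likely damage is moderate: about 5.2% to 8.0% in place of 5.0% for a between-group comparison of provider-level values. This rests on a true ICC of 0.04, 74 equal clusters of 8, one value per provider, two-sided testing, and assumed cut-offs. For the time-by-group contrast, ignoring the level could cost nothing or raise the error to about 10%, depending on how stable the cluster effect is over time. It would be wrong to conclude that standard errors in this trial will be too small; they can be, if the level is dropped while the true ICC is above zero.

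**What to change.** In the general data analytic plan, delete the sentence that makes accounting for clustering depend on the ICC. State instead that every provider- and child-level comparison of conditions keeps the program/district random effect whatever the estimated ICC, and that ICCs are reported descriptively only. In the aim 2 section, limit the single-level alternative to analyses with one record per program or district.

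This changes a few sentences. It needs no additional participants, because both sample-size figures already include the VIF of 1.28. The cost is slightly wider intervals if the true ICC is near zero.
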